## Abstract

**Background:**

Type 2 respiratory failure (T2RF) is a common and high-risk presentation in the emergency department (ED). Noninvasive positive pressure ventilation (NIPPV) is a standard first-line therapy for T2RF, particularly in acute exacerbations of chronic obstructive pulmonary disease and cardiogenic pulmonary edema. However, NIPPV has limitations, including discomfort, claustrophobia, air leaks, skin injury, and aspiration that may compromise tolerance and lead to treatment failure or escalation to endotracheal intubation. High-velocity nasal insufflation (HVNI), particularly via a single-prong asymmetric cannula configuration, has been proposed to enhance dead-space washout and improve patient comfort. Despite growing interest, robust evidence of evaluation of HVNI in heterogeneous, all-cause T2RF populations in the ED remains limited.

**Objective:**

This study aims to determine whether HVNI delivered via a single-prong nasal cannula is noninferior to standard NIPPV in improving ventilation among adult ED patients with T2RF from any cause.

**Methods:**

This is a single-center, open-label, noninferiority randomized controlled trial conducted in the ED of a tertiary academic center. Adults aged 21 years and above with T2RF, defined as partial pressure of carbon dioxide (PaCO_2_) above 45 mm Hg and pH below 7.35 requiring ventilatory support, will be randomized 1:1 to HVNI via a single-prong cannula or standard NIPPV. Allocation will be concealed via an independent web-based platform using variable block sizes. The primary outcome is percentage change in PaCO_2_ from baseline to 60 minutes after initiation of therapy. A total of 84 patients provide 80% power and one-sided α of 2.5% assuming an SD of 6.65% and noninferiority margin of 4.3%. Analyses will use intention-to-treat and per-protocol approaches, and sensitivity analyses to address missing arterial blood gas results will be conducted. Predefined failure criteria (persistent or worsening acidosis, rising PaCO_2_, refractory hypoxemia, severe intolerance, and clinical deterioration) will trigger crossover or escalation per protocol.

**Results:**

Ethics approval was granted by the local institutional ethics board on February 24, 2025 (reference 2024-4329). Recruitment commenced in January 2026 and is expected to be completed by June 2027. As of July 2026, a total of 19 participants have been enrolled out of a target sample of 84. Data analysis will commence following completion of enrollment, with results expected to be published by 2028.

**Conclusions:**

Should HVNI via a single-prong cannula be shown to be noninferior to NIPPV, it may offer a practical alternative to treatment of T2RF in the ED when mask-based interfaces are poorly tolerated or contraindicated, potentially reducing the need for more invasive interventions such as endotracheal intubation and mechanical ventilation.

## Introduction

Acute respiratory and cardiac conditions are frequently encountered in the emergency department (ED), ranging from mild to life-threatening presentations. Among patients who are critically ill, a substantial proportion present with hypercapnic, or type 2, respiratory failure (T2RF) [1]. Common etiologies include acute exacerbations of chronic obstructive pulmonary disease (COPD), pneumonia, congestive cardiac failure, restrictive lung disease, neuromuscular disease, and opioid or benzodiazepine use [2]. Early, effective ventilatory support in the ED can improve patient-centered outcomes by reducing work of breathing, correcting gas exchange, and potentially averting endotracheal intubation [3].

Noninvasive positive pressure ventilation (NIPPV) is a standard first-line treatment modality for T2RF, particularly in COPD exacerbations and cardiogenic pulmonary edema [4]. By providing inspiratory positive airway pressure (IPAP) and expiratory positive airway pressure (EPAP), NIPPV improves ventilation, reduces the work of breathing, and can correct acidosis. However, NIPPV has limitations that can affect effectiveness and tolerance, including mask-related discomfort and claustrophobia; nasal bridge skin abrasions; dry and nonhumidified air resulting in airway mucosal injury; gastric distension; aspiration; air leaks; and challenges with secretion clearance, oral intake, and communication, which may lead to therapeutic failure [5,6]. Treatment failure often necessitates endotracheal intubation, with its attendant risks such as peri-intubation hypotension and cardiac arrest and longer-term risk of ventilator-associated complications [7].

High-flow nasal therapy delivers heated, humidified gas at high flow rates via nasal cannula. Compared to conventional low-flow oxygen, it improves comfort and tolerance, provides a small degree of positive airway pressure, reduces entrainment of room air, and may decrease the metabolic cost of conditioning inspired gas [8]. In hypoxemic respiratory failure, high-flow therapy has been associated with reduced intubation compared to conventional oxygen [9,10]. In contrast, evidence in T2RF is mixed and has focused largely on COPD, with uncertainty about the equivalence or superiority relative to NIPPV [11].

High-velocity nasal insufflation (HVNI) is a specific implementation of high-flow therapy that uses smaller-bore cannulae to deliver higher-velocity flow, generating greater nasopharyngeal pressure at comparable flow rates and enhancing washout of extrathoracic dead space [12]. Early studies suggest that HVNI may be noninferior to NIPPV for composite outcomes such as the need for intubation in mixed populations, with preliminary subgroup findings in patients with T2RF; however, these analyses are limited by design (eg, subgroup or post hoc) and predominance of COPD [13,14]. A single-prong asymmetric-flow nasal cannula design (Unicorn; Vapotherm Inc) has been proposed to facilitate carbon dioxide (CO_2_) egress and improve dead-space clearance at lower total flow rates, which may be advantageous for patients with unilateral nasal patency, facial trauma, or indwelling tubes [15]. Clinical trial data demonstrating ventilation benefits of such single-prong HVNI in T2RF are currently lacking.

While high-flow modalities are generally well tolerated, they are not without risk. Reported adverse effects include nasal dryness or irritation, epistaxis, and rare barotrauma [16,17]. Other considerations include infection control and aerosol generation, which depend on interface fit and clinical context [18,19]. Balanced against the known limitations and intolerance of NIPPV, there is a clear rationale to test whether HVNI can provide comparable ventilatory efficacy in the ED while maintaining better tolerability.

This noninferiority randomized controlled trial is designed to determine whether HVNI delivered via nasal cannula in a single-prong configuration is noninferior to NIPPV for improving ventilation in ED patients with T2RF from any cause. We hypothesize that HVNI will be noninferior to NIPPV with respect to reduction in partial pressure of CO_2_ (PaCO_2_) over an early, clinically relevant time frame, with secondary outcomes including intubation, treatment tolerance, and safety.

## Methods

### Study Design and Setting

This will be a single-center, noninferiority, open-label randomized controlled trial conducted in the Emergency Medicine Department of National University Hospital, Singapore, a 1225-bed tertiary academic medical center with 24/7 specialist coverage and approximately 110,000 annual attendances. Adult patients aged 21 years and above requiring NIPPV for T2RF due to any cause will be randomized to HVNI or NIPPV. The trial has been registered in ClinicalTrials.gov (NCT07065656). The protocol was prepared in accordance with the SPIRIT (Standard Protocol Items: Recommendations for Interventional Trials) 2025 statement [20]. The SPIRIT participant timeline is shown in Figure 1.

**Figure 1. F1:**
[figure not shown]
SPIRIT (Standard Protocol Items: Recommendations for Interventional Trials) 2025 schedule of enrollment, interventions, and assessments for a noninferiority randomized controlled trial. *Emergency waiver with delayed consent may be obtained from the patient or legally acceptable representative at the earliest opportunity.

### Ethical Considerations

This study received ethics approval from the National Healthcare Group Domain Specific Review Board (reference 2024-4329) on February 24, 2025. Because patients with T2RF are deemed critically ill and hypoxia may affect their mental capacity, informed consent will be obtained from a legally acceptable representative (LAR) where feasible prior to randomization. If an LAR is unavailable and enrollment cannot be delayed, patients will be enrolled under emergency waiver, with delayed consent obtained from the LAR or the patient at the earliest opportunity prior to hospital discharge. This approach complies with Singapore’s regulations for clinical trials under emergency situations [21]. The waiver and delayed consent will be certified by a study investigator and an independent emergency medicine specialist. Individual participant data will be deidentified prior to sharing.

### Eligibility Criteria

Adult patients aged 21 years and above with T2RF, defined as arterial blood gas (ABG) showing PaCO_2_ above 45 mm Hg with pH below 7.35 due to any cause for whom ventilatory support is indicated in the ED will be included. Patients with do-not-resuscitate orders are eligible if NIPPV use is permitted. The clinical indications for initiating ventilatory support are identical for both HVNI and NIPPV in this trial as both modalities target the same pathophysiology of acute hypercapnic respiratory failure requiring augmented ventilation. The following patients will be excluded: patients with do-not-resuscitate orders that specifically do not allow for NIPPV, clinical suspicion or confirmed base of skull fracture or severe facial trauma precluding mask or cannula placement, vulnerable patient populations (eg, pregnant women or prisoners), refusal of consent (by the patient or LAR), hemodynamic instability requiring immediate resuscitation (eg, systolic blood pressure <90 mm Hg after initial fluids), cardiac or respiratory arrest, and immediate need for endotracheal intubation as judged by the attending physician. Additional exclusion criteria include contraindications specific to either modality: complete nasal obstruction or anatomical abnormalities precluding nasal cannula placement (contraindication to HVNI), recent upper-airway or esophageal surgery (contraindication to both NIPPV and HVNI), undrained pneumothorax (contraindication to positive pressure ventilation), active uncontrolled upper gastrointestinal bleeding with high aspiration risk, and inability to protect the airway (eg, excessive secretions with absent cough reflex).

### Randomization and Allocation Concealment

Enrollment will be through convenience sampling of eligible ED patients triaged as “urgent” or “immediate.” All study investigators are full-time clinicians with an average of 16 to 20 shifts per month to cover as many shifts as possible for enrollment. Participants will be randomized 1:1 to HVNI or NIPPV using variable block sizes generated by an independent web-based platform [22]. The specific block sizes are not disclosed in this manuscript to prevent prediction of the allocation sequence. Allocation will be implemented via sealed, opaque, sequentially numbered envelopes, with allocation concealment maintained until randomization is completed.

### Blinding

Due to the nature of the interventions, participants, treating clinicians, and bedside nursing staff cannot be blinded to group allocation. ABG is analyzed at the bedside using i-STAT Alinity (Abbott Laboratories). Device allocation will not be recorded on ABG stickers or forms to minimize detection bias. The data analyst performing the primary and secondary outcome analyses will also be blinded to treatment allocation and will receive deidentified datasets with treatment arms coded (eg, group A and group B) without revealing the intervention assignment. Data entry staff who are not involved in clinical care will be trained to abstract outcomes using standardized case report forms (CRFs). Nevertheless, the primary outcome evaluated is objective and should not be confounded by lack of blinding [23].

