### Interventions

In the HVNI arm, patients will receive oxygen therapy through the Vapotherm high-velocity therapy 2.0 via a single-prong nasal cannula (Unicorn). Initial settings are flow rate of 35 L per minute [14], temperature of 37 °C, and fraction of inspired oxygen (FiO_2_) titrated up to 1.0 to achieve target oxygen saturation (SpO_2_). The titration algorithm will be to maintain flow rate at 35 L per minute when tolerated to optimize CO_2_ washout. If intolerance occurs (eg, agitation or discomfort), stepwise reduction in flow by 5 L per minute will be performed to the minimally tolerated level while maintaining target SpO_2_. Adjustments in temperature and FiO_2_ will be up to the attending physician’s discretion to achieve the target SpO_2_ value. Flow rate may be uptitrated as tolerated upon assessment of respiratory rate, work of breathing, and comfort. Study investigators will verify that the single-prong cannula remains securely positioned in the nostril and has not been dislodged due to patient movement. Mouth state (open vs closed) will be recorded at each assessment time point as open-mouthed breathing may reduce the effectiveness of nasopharyngeal dead-space washout. If the cannula is found to be displaced, it will be repositioned immediately, and the event will be documented. Persistent inability to maintain cannula position will be recorded as a protocol deviation.

In the NIPPV arm, patients will receive ventilation through the Respironics V60 respirator (Philips Healthcare) with an oronasal mask of appropriate size. Initial settings are IPAP of 12 to 20 cm H_2_O, EPAP of 5 to 10 cm H_2_O, and FiO_2_ of up to 1.0 to achieve the target SpO_2_. The titration algorithm will be to adjust IPAP to alleviate dyspnea and reduce respiratory rate and PaCO_2_, adjust EPAP for oxygenation and to counter intrinsic positive end-expiratory pressure when indicated, and optimize mask fit to minimize leak.

Cointerventions such as bronchodilators, systemic steroids, antibiotics, diuretics, and other standard-of-care therapies are permitted as clinically indicated and should follow departmental protocols. To reduce confounding, all cointerventions will be documented with time stamps. Initiation of major therapy changes will be avoided within 10 minutes preceding scheduled ABG draws when clinically safe.

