### Oxygen Targets and Monitoring

All patients will be put on continuous pulse oximetry. For presumed acute respiratory acidosis without known chronic hypercapnia, SpO_2_ will be maintained above 95%, and for known or suspected chronic hypercapnia with acute decompensation, SpO_2_ will be kept between 88% and 92%. Each patient’s target range will be declared at baseline and maintained throughout the initial 60-minute assessment window unless clinical changes require adjustment. FiO_2_ will be titrated to maintain the declared target. Physiologic monitoring will include vital signs per ED standard, with respiratory rate recorded at baseline, 30 minutes, and 60 minutes.

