### Outcome Measures

The primary outcome is the percentage change in PaCO_2_ from baseline to 60 minutes after initiation of therapy. Baseline is defined as the pretreatment ABG obtained before initiation of the assigned therapy (HVNI or NIPPV). This ensures that the primary outcome reflects the ventilatory effect of the intervention itself. The 30- and 60-minute assessment time points are measured from the time of therapy initiation. The ABG results and other variables (Table 1) to be collected will be documented in real time on paper-based CRFs by trained study investigators.

**Table 1. T1:** Summary of recorded patient variables in a noninferiority randomized controlled trial comparing high-velocity nasal insufflation (HVNI) vs noninvasive positive pressure ventilation (NIPPV) for type 2 respiratory failure in adult emergency department patients at National University Hospital, Singapore.

Variables	Measure
Primary outcome measure	Change in PaCO_2_^a^ at 60 min obtained after initiation of HVNI or NIPPV compared to baseline (before initiation of therapy)
Secondary outcome measures	Change in PaCO_2_ at 30 min compared to baseline Changes in respiratory rate 30 and 60 min after initiation of HVNI or NIPPV Modified Borg Dyspnea Scale at 30 and 60 min Treatment failure Conversion to another modality of oxygenation Requirement for intubation in the emergency department Adverse events due to therapy
Demographics	Age Gender Ethnicity BMI
Comorbidities	Congestive cardiac failure Ischemic heart disease Atrial fibrillation Chronic obstructive pulmonary disease Asthma Obstructive sleep apnea Diabetes mellitus Bronchiectasis Restrictive lung disease Neuromuscular disease Opioid or benzodiazepine use
Vital signs	Temperature Heart rate Respiratory rate Systolic and diastolic blood pressure Mean arterial pressure Glasgow Coma Scale
Investigations	Chest x-ray findings Arterial blood gas results at 0, 30, and 60 min
Clinical course and secondary clinical outcomes	Emergency department diagnosis Hospital inpatient discharge diagnosis Length of intensive care unit stay (if any) Length of hospital stay Inpatient mortality

a PaCO_2_: partial pressure of carbon dioxide.

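### The objective blood gas guards the 60-minute outcome against measurement bias only; unblinded choices of cointervention and oxygen-target group can still differ by arm, and the protocol should say so and fix the target group before allocation

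*Protocol article*

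**What the plan says.** All references are to the protocol article.

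- **Blinding.** The section states that "participants, treating clinicians, and bedside nursing staff cannot be blinded to group allocation". Its safeguards are that the device is not written on blood-gas forms, the arms are coded for the analyst, and abstraction is done by staff outside clinical care. It concludes that "the primary outcome evaluated is objective and should not be confounded by lack of blinding".
- **Outcome Measures.** The primary outcome is the percentage change in PaCO2 "from baseline to 60 minutes after initiation of therapy". Of the pretreatment baseline gas, the section says: "This ensures that the primary outcome reflects the ventilatory effect of the intervention itself".
- **Interventions.** Bronchodilators, steroids, antibiotics, diuretics and other standard therapies may be given on clinical indication and should follow departmental protocols. "To reduce confounding, all cointerventions will be documented with time stamps". Major therapy changes are to be avoided in the 10 minutes before a scheduled gas, when that is clinically safe.
- **Oxygen Targets and Monitoring.** One SpO2 range (above 95%) is for presumed acute acidosis where chronic hypercapnia is not known. The other (88% to 92%) is "for known or suspected chronic hypercapnia with acute decompensation". The range is "declared at baseline and maintained throughout the initial 60-minute assessment window unless clinical changes require adjustment".
- **Quality Assurance and Monitoring.** Quarterly checks cover device settings, oxygen targets, gas timing and cointervention records.
- **Discussion.** Performance bias is named in connection with clinician-driven decisions, and predefined rescue and intubation criteria are the remedy offered. The limitations concede that lack of blinding may affect subjective measures and escalation decisions, and again offer the objective end point as mitigation.

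**The concern.** An objective assay prevents detection bias: knowing the device cannot change what the analyzer prints. It does not prevent performance bias, in which knowing the device changes the care given before the sample is drawn. PaCO2 at 60 minutes results from the device, the drugs and the oxygen management together. The Interventions section accepts this when it treats cointerventions as a source of confounding, so the broad sentence under Blinding does not sit well with the protocol's own text.

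Two decisions are open to people who know the arm. One is which cointerventions are given in the window, and when. The other is the classification that selects the oxygen range, which also feeds the SpO2 criterion for treatment failure under Rescue, Failure, and Crossover Criteria. If either differs by arm, the HVNI–NIPPV difference is no longer the effect of the device alone. The noninferiority test then compares two packages of care against a margin of only 4.3 points.

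**Working it through.** **1. What each safeguard covers**

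| Safeguard | Section | Protects against | What it leaves open |
|---|---|---|---|
| Arm not on gas forms; coded arms; separate abstractors | Blinding | Measurement, abstraction and analysis bias | Care between 0 and 60 minutes |
| Departmental protocols | Interventions | Wide variation in drug use | The judgement that a drug is indicated |
| Time stamps | Interventions | Loss of information | They record unequal care but do not equalise it |
| 10-minute quiet periods | Interventions | Late changes before a gas | See step 2; also waived when not clinically safe |
| Target declared at baseline and held | Oxygen Targets and Monitoring | Drift after declaration | The classification itself, its timing relative to allocation, and the adjustment clause |
| Quarterly checks | Quality Assurance and Monitoring | Poor adherence and missing records | Permitted care that differs by arm |
| Rescue criteria | Rescue, Failure, and Crossover Criteria; Discussion | Arbitrary escalation | Cointerventions and target classification |

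**2. Exposed time.** Gases after the start of therapy are scheduled at 30 and 60 minutes. Two quiet periods of 10 minutes leave 60 − 2 × 10 = 40 minutes open.

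**3. Overlapping categories.** A patient in whom chronic hypercapnia is suspected but not known meets the first description (not known) and the second (suspected). Both ranges then apply on the wording, and the choice falls to the clinician.

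**4. Timing.** The target is declared at baseline. The only definition of baseline, under Outcome Measures, concerns the blood gas and is relative to the start of therapy. Allocation is revealed by envelope (Randomization and Allocation Concealment). No sentence places the declaration before the envelope.

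**5. Would the planned analyses reveal it?** The ANCOVA covariates given as examples (etiology, baseline pH, age) and baseline PaCO2 are all baseline variables. The per-protocol set excludes major deviations, with early crossover and missing gases as examples. A permitted cointervention is not a deviation, so unequal use passes through both analyses.

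**6. The plan's sample size, reproduced.** Inputs from Sample Size: SD 6.65, margin 4.3, one-sided alpha 2.5%, power 80%, 10% allowance; true difference taken as 0.

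n per arm = 2 × [6.65 × (1.960 + 0.842) / 4.3]² = 37.54, so 38 evaluable. 37.54 / 0.9 = 41.7, so 42 per arm and 84 in total. The stated figure is reproduced.

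**7. Illustration of size.** The documents give no bias, so b below is assumed. With 38 evaluable per arm, SE = 6.65 × √(2/38) = 1.53 points.

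- Bias favouring HVNI, true deficit equal to the margin: chance of a false claim = Φ(b/SE − 1.96).
- Bias against HVNI, true difference 0: power = Φ((4.3 − b)/SE − 1.96).

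| Assumed b (points) | False noninferiority if b favours HVNI | Power if b is against HVNI |
|---|---|---|
| 0 | 2.5% | 80.5% |
| 0.5 | 5.1% | 70.2% |
| 1.0 | 9.6% | 58.0% |
| 1.43 | 15.3% | 46.9% |
| 2.0 | 25.8% | 32.5% |

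For scale, 1 mm Hg at the protocol's example baseline of 70 mm Hg is 1/70 = 1.43 points, and 1 point is 1.0/4.3 = 23% of the margin. If all 42 per arm contribute, SE is 1.45, and b = 1.0 gives 10.2% and 62.3%.

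**The case against.** The strongest reply is that the sentence closes a paragraph about measurement and analysis, cites a source that is not available here, and says the outcome should not be confounded, not that it cannot be. Read in that place, it may be meant only as a statement about detection bias. The reply continues that the protocol knows about performance bias: it ties cointerventions to departmental protocols in both arms, sets the oxygen ranges by rule, holds the declared range for the hour, checks both quarterly, and discusses the issue. Unblinded care is also inherent in an open-label device trial.

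Much of this stands. It narrows the room for bias and rules out a charge that the protocol ignores it. It does not rescue the sentence as worded, because the Discussion confines its concession to subjective measures and escalation and uses the objective end point again as the answer. It also does not settle the overlap in the target categories.

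Four stronger readings are tempting and are not supported:

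- *The bias favours noninferiority.* Staff might treat the HVNI arm harder, but they might equally titrate the familiar device harder. The documents give no direction.
- *The oxygen target is set after allocation is known.* The article does not say this. It only fails to exclude it, and the full protocol may fix the order.
- *Sedatives or reversal agents distort the comparison.* The cointervention text names neither.
- *The time stamps will go unused.* Tables and further sensitivity analyses may be in a statistical analysis plan that is not shown, so their absence here is not an error.

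**Conclusion.** The concern holds in a limited form. The Blinding section claims more than an objective assay can deliver. Cointerventions and the oxygen-target classification remain open to influence by knowledge of the arm for most of the primary window, and the two planned analysis sets would not show it. The overlap between the target categories is a defect on the face of the text.

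The size is unknown. The 1-point illustration (2.5% to about 9.6% if the bias favours HVNI; power of about 80% to 58% if it runs against) rests on an assumed bias, the planned SD, a normal approximation and 38 evaluable patients per arm. It shows that a modest imbalance matters against this margin, not that one will occur. The effect of the oxygen target on PaCO2 is likewise an assumption: the protocol implies it by giving chronic hypercapnia a separate range, but does not state it. The sample size of 84 is not in question.

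**What to change.** 1. Limit the Blinding sentence to measurement bias. Add that care in the first 60 minutes is given unblinded and may differ by arm, and extend the Discussion's concession to cover it. Under Interventions, describe time stamps as documenting cointerventions, not as reducing confounding.
2. Have the oxygen-target group and the planned initial cointerventions written on the CRF before the envelope is opened. Eligibility already requires a qualifying blood gas and a decision to ventilate. Log later changes with time and reason.
3. Add the pre-allocation target group to the ANCOVA covariates. This accounts for chance imbalance in the group; it does not correct unequal care afterwards.
4. Tabulate 0 to 60 minute cointerventions by arm, unless the statistical analysis plan already does so.
5. Reconcile the two oxygen-target categories so that a suspected but unconfirmed case falls in only one. Which range applies is for the investigators.

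An analysis that excludes patients because of a drug given in the window should not be added, or should be labelled supportive only: it conditions on an event after randomisation that the device may influence, and so can create selection bias.

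The cost is a few seconds before allocation and slightly more CRF work. The article reports 19 of 84 enrolled, so the procedure could cover up to 65 participants. For those already enrolled, state whether the target was recorded before or after allocation, or that this is not known.
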